
### Step 4: Evaluation

#### Evaluation Framework.

The evaluation of this research will be conducted within an overarching conceptual framework that combines key constructs from the RE-AIM Framework [43] with the Health Equity Implementation Framework [44]. The evaluation variables are outlined in Table 1. During the co-design process services may identify additional variables or research questions of interest to their unique context and these will be added to the evaluation framework. Quantitative data will be used to assess intervention impact, interpreted alongside an understanding of how colonial health structures shape outcomes. Indigenist qualitative methods will provide context, centring participants’ experiences, voices, and definitions of meaningful change. Evidence of “success” will be judged equally by increases in the primary outcome toward cervical screening elimination targets (i.e., 70% participation) and by the extent to which participants define the co-design and implementation phases as “successful”, including the degree to which these practices embody sovereignty and support health system (re)build.

**Table 1 pone.0336004.t001:** Evaluation variables.

Approach	Collection methods	Variables
Quantitative	• De-identified data extracted from service Record Management Software and/or Clinical Audit Tools at baseline (#T0), periodic intervals as determined by each service (approximately 3 monthly), and 12 months for pre-post analysis (#T1). Services can provide data at 3 and 6 months post implementation.	De-identified cervical screening data for screen eligible Aboriginal and Torres Strait Islander clients at each service (number and proportion): • Cervical screening participation #T0, #T1 • Under-or never-screened #T0, #T1 • Cervical screens by collection method (i.e., self- or clinician-collection) #T1 • HPV positive tests #T1
Qualitative	• Qualitative Yarns and Yarning circles with ACCHO staff and eligible clients (women and people with a cervix)	• Yarns will cover topics such as: experience of participating in or implementing strategies; perceptions of effectiveness; reach and sustainability of strategies; challenges and strengths throughout implementation period.

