### Data collection and analysis

#### Cervical screening data.

The primary outcome will be the number and proportion of Aboriginal and Torres Strait Islander women and people with a cervix who are overdue for cervical screening (under-screened) or have no recorded history of a cervical screen (never-screened) at the completion of the study, compared to the before period. Secondary outcomes are cervical screening participation, the number and proportion of cervical screens conducted by collection type (self-collect versus clinician collect) and HPV positive tests in the 2-years before and during the study period. Quantitative outcomes data will be obtained using one or a combination of the following pathways to be determined by the services’ preferences: from local practice management software, practice audit tools, from the National Cervical Screening Register (NCSR) and/or manual audit of relevant patient records. De-identified data will be provided to nominated members of the research team via secure methods.

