### Analysis

Primary and secondary outcomes will be calculated comparing data from the before (*T0*) and after (*T1*) period. Retention of effects will be measured for services who provide data at 3- and 6-month intervals in the post-implementation period. For the primary outcome, the number and proportion of all screen eligible clients at the services who are under-screened or never-screened at *T1* compared to *T0* (number of under- and never-screened screen eligible clients/number of screen eligible women). Secondary outcomes are cervical screening participation rate (number with a recorded cervical screen in the previous 5-years/number of screen eligible clients), and the number and rate of cervical screens conducted using self-collection (number of tests conducted using self-collection/number of screening tests), and the HPV positivity (number of HPV positive tests/number of screening tests). Descriptive analysis will be used to analyse cervical screening data, with regular interim reports made available to participating services. Primary and secondary outcomes will be calculated comparing data from the before (T0, > 24 months) and after (T1, 12 months) period. The before and after intervention periods will be compared descriptively, and using multi-level logistic regression models clustered on site and allowing for participants who are active in both periods. Due to the small number of participating services, modelled findings and secondary subgroup analyses will be interpreted cautiously, with emphasis on direction and magnitude. A subgroup analysis will also be conducted of the primary outcome among women who have never screened or screened >10 years ago. These will be considered exploratory with no adjustment for multiplicity planned given the implementation focus. Data will be analysed using Microsoft Excel (Microsoft Corporation) and STATA software (StataCorp, version 18).

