### Sample size

As per clinical guidelines, any women and people with a cervix who have not screened under the new HPV screening program will be considered under screened (at least four years overdue); this equates to about 50% or more of eligible screen eligible clients at the services. The baseline screening rate assumption is that 5–10% of screen eligible women and people with a cervix currently move from under screened to screened per 12 months; assuming an increase with policy change to open access to self-collection in 2022 (prior to study intervention) to 20% per 12-month period. To detect a doubling in participation among under screened women and people with a cervix, from 20% in 12 months at baseline to 40%, with 80% power (2-alpha = 5%) and a conventional non-clustered design, would require 91 women and people with a cervix per arm. Allowing up to 12 clusters before and after, and assuming a conservative Intraclass correlation coefficient (ICC) of 0.1, then an average of 50 women and people with a cervix per cluster per period would give a design effect of 5.9, so a total of 1074 women and people with a cervix are required, rounding up to 1200 women and people with a cervix (600 before period, 600 after period). This is feasible given the typical service populations of ACCHOs and the chosen jurisdictions.

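### Screens by collection type are counted over 24 months or more before and 12 months after, with no time denominator, so a doubling of monthly activity shows at best as no change in the count

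*Protocol article*

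**What the plan says.** Four places in the protocol article bear on this.

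- **Analysis.** The windows are set for all outcomes together: "Primary and secondary outcomes will be calculated comparing data from the before (T0, > 24 months) and after (T1, 12 months) period". The same section lists "the number and rate of cervical screens conducted using self-collection" as a secondary outcome. Its formula for that rate is self-collected tests over all screening tests, so it is a share of tests and not a rate over time. HPV positivity is likewise defined per screening test.
- **Data collection and analysis, Cervical screening data.** The secondary outcomes cover screens split by how the sample was taken, as both a count and a proportion. The list closes with "HPV positive tests in the 2-years before and during the study period". The before window is given here as two years, and in the Analysis section as more than 24 months.
- **Table 1 (Evaluation Framework).** The quantitative variables are headed "De-identified cervical screening data for screen eligible Aboriginal and Torres Strait Islander clients at each service (number and proportion"). Participation and under- or never-screened status are marked for both T0 and T1. Collection method and HPV-positive tests are marked for T1 only.
- **Sample size.** The planned contrast is on equal periods: "from 20% in 12 months at baseline to 40" per cent, also over 12 months.

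**The concern.** A count accumulates with time. If events are counted for at least twice as long before as after, the before count has an advantage of at least two to one that has nothing to do with the strategies. The text makes numbers, as well as proportions, before-versus-after outcomes. It fixes the two windows at different lengths and supplies formulas with no time in them.

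Direction and magnitude are at stake. The Analysis section plans a descriptive comparison of the periods and, because few services take part, says that modelled results will be read mainly for direction and size. Set side by side as raw totals, the counts would give the wrong direction, or hide a rise, for any true increase up to a doubling or beyond.

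**Working it through.** **Inputs.** After window: 12 months (Analysis; this matches the 12-month implementation in Step 3). Before window: two years (Cervical screening data) or more than 24 months with no upper limit (Analysis). Target effect: 20% to 40% per 12 months (Sample size). Before-window lengths of 27, 30 and 36 months are assumptions that show the range the open-ended wording allows.

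**The plan's own figure.** For 20% versus 40%, two-sided 5% and 80% power, the two-proportion formula gives 82 per arm without and 91 with continuity correction. The design effect is 1 + (50 − 1) × 0.1 = 5.9, and 2 × 91 × 5.9 = 1073.8, rounded up to 1074. The stated 91 and 1074 are reproduced. They rest on equal 12-month periods.

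**Count ratio.** Let the monthly rate be r before and RR × r after, with a stable eligible population.

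After/before count ratio = (RR × r × 12) / (r × B) = RR × 12/B, where B is the before window in months.

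| B (months) | RR = 1 | RR = 1.5 | RR = 2 | RR needed for the count to rise at all |
|---|---|---|---|---|
| 24 | 0.50 | 0.75 | 1.00 | above 2.0 |
| 27 (assumed) | 0.44 | 0.67 | 0.89 | above 2.25 |
| 30 (assumed) | 0.40 | 0.60 | 0.80 | above 2.5 |
| 36 (assumed) | 0.33 | 0.50 | 0.67 | above 3.0 |

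Dividing each count by its own months gives RR itself in every row: 1, 1.5 and 2.

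**Illustration on the plan's scale.** Treat the planning rates purely as a constant yearly flow of screens in 600 people. Before: 600 × 0.20 × 2 years = 240. After: 600 × 0.40 × 1 year = 240. An effect of the size the study was planned to detect leaves the count unchanged. With an assumed 36-month before window, the figures are 600 × 0.20 × 3 = 360 against 240.

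**Outcomes that do not depend on window length.**

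- The primary outcome is the proportion under- or never-screened at T1 compared with T0, which is a status.
- Participation has its own five-year look-back at both time points.
- The self-collection share and HPV positivity have screening tests as denominator. An illustrative constant share of 30% is 30% over 12, 24 or 36 months, because numerator and denominator grow together.

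**The case against.** The strongest case on the other side has four parts.

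1. **The affected set is small.** The logistic models do not analyse raw counts, and the primary outcome and all the ratio outcomes are untouched. Total screens is not a separately named outcome; it is only the sum of the counts by type. HPV positivity in the Analysis section is a ratio, so an HPV-positive count rests on the outcome list and the Table 1 header. All of this stands and sets the limits of the point.

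2. **Table 1 schedules collection method and HPV-positive tests at T1 only.** Under that table there would be no before count to compare. This is fair, but it contradicts the two sections that do state a before-and-after comparison. It is a second thing to reconcile, not an answer to the first.

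3. **A condensed article may leave annualising to the full plan.** A plan not shown might indeed annualise. The point is not that detail is missing, however. The article states unequal windows and gives time-free formulas.

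4. **Nothing says that services will be sent a 24-month total set against a 12-month total.** That is correct. The article promises interim reports without describing their layout, so harm through those reports is possible but not shown.

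Two stronger readings are tempting and should be resisted. One is that the unequal windows bias the primary outcome or the study's main conclusion; the definitions above rule out a mechanical bias of that kind. The other starts from the planning rate: 20% a year compounds to 1 − 0.8² = 36% over 24 months, so the planned contrast would shrink to 36% versus 40%. That would need an outcome defined as being screened at some time during the period, and neither outcome section defines one. It also assumes a fixed group with a constant, independent yearly probability.

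**Conclusion.** The point holds for the numbers of self-collected and clinician-collected screens and, on the outcome list and the Table 1 header, for the number of HPV-positive tests. Compared as written, the raw count ratio understates the monthly rate ratio by a factor of two if the before window is 24 months, and by more if it is longer. The two-fold figure follows from the stated windows. Anything beyond it depends on an upper limit that the text does not give. The arithmetic assumes a stable eligible population and steady rates within each window.

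The affected counts are secondary and descriptive, so the trial's main result is not at risk. The correction is still worth making, because the distortion can reverse the apparent direction of change and is easily removed before results, which are expected in 2027.

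**What to change.** In the Cervical screening data and Analysis sections:

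- Give T0 one fixed length. Two years and more than 24 months are not the same window.
- Compare counts as rates per unit of time, for example screens, self-collected screens and HPV-positive tests per 100 screen-eligible clients per 12 months. Keep all before-period data. There is no need to discard earlier months, least of all for the per-test proportions, which have no length problem.
- As a sensitivity analysis, compare the 12 implementation months with an equal 12-month before window matched on calendar months. State whether that window includes the co-design phase. Co-design is expected to last about six months, so a window ending at implementation start could be up to half co-design time, when services are already engaged with cervical screening.
- Reconcile Table 1 with the text: either mark collection method and HPV-positive tests for T0 as well as T1, or drop the before-and-after comparison of those items.

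The cost is a wording change, a little extra tabulation, and a person-time or eligible-client denominator for the before period at each service. That denominator is the only new data requirement.

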### Step 1: Recruitment of services to participate in *Screen Your Way*

A minimum of six services (two per jurisdiction) will be recruited, using a process similar to that used successfully with ACCHOs in the literature [38,39]. Support to approach services about participation in the research has been obtained from relevant community-controlled National and State-based governing bodies, including National Aboriginal Community Controlled Health Organisation (NACCHO), Queensland Aboriginal and Islander Health Council (QAIHC), Aboriginal Health and Medical Research Council (AHMRC) of NSW and Aboriginal Medical Services Alliance Northern Territory (AMSANT). Services will be invited to submit an expression of interest. The communication avenue(s) used will through existing networks and guided by QAIHC, AMSANT and AHMRC but will likely include contact through their member email lists and newsletters (usually sent to service Chief Executive Officers, Medical Directors and/or Boards).

Services will be purposefully sampled in line with the following eligibility criteria:

1.Are an ACCHO, or a primary healthcare organisation with a majority of clients being Aboriginal and Torres Strait Islander people whose context is similar to that of an ACCHO (referred to as ACCHOs hereinafter)2.Are located in Qld, NSW or the NT3.Have 120 or more Aboriginal and Torres Strait Islander women or people with a cervix aged 25–74 years who are active clients (defined as three or more clinic visits in past two years)4.Have at least one cervical screening certified health professional5.Consent to provide screening data related to cervical screening.

Services will be excluded if they are unable to meet the inclusion criteria or if they are involved in other trials relating to cervical screening given the potential to contaminate results.

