### Step 2: Co-design of strategies for implementing self-collection at each site

We will work with nominated staff at participating services to facilitate co-design workshops, set priorities collaboratively, and design locally tailored strategies, engaging community members as determined by each service. This process will follow key principles of co-design with Aboriginal and Torres Strait Islander peoples, including leadership, cultural grounding, respect, benefit to community, inclusive partnerships, transparency, evaluation, and reciprocity [40,41].

Co-design will occur through a structured yet flexible and iterative process facilitated by the research team and tailored to each site. We will begin by meeting with nominated service staff, often those involved in cervical screening or research, to agree on the preferred approach and identify who should participate, such as other clinical staff, non-clinical staff, and local community members or groups. Each site will be offered up to two in-person visits; however, workforce availability and geographic challenges may mean many engagements occur online, supplemented by virtual planning meetings and collaborative workshops.

While co-design will be guided by each service, it will broadly address local priorities and goals for cervical screening, explore context, identify barriers and facilitators, and develop strategies to enhance access. These ideas will be refined into implementation strategies through multiple interactions between the research team and service staff. This iterative approach allows strategies to evolve in response to feedback and context, ensuring each solution is tailored to the unique needs of the service. In practice, this means strategies may iteratively develop over the course of the implementation period as new priorities are identified. There will be no predetermined list of strategies; all ideas will emerge through co-design to support local needs. However, a common focus across sites will be improving data support and access. Strategies to achieve this will vary depending on local systems and capacity. All strategies will aim to increase participation of under- and never-screened women and people with a cervix in cervical screening using HPV self-collection. Strategies may include community engagement, participant-level interventions, workforce development, and system or service-level changes.

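### The model in the Analysis section names site and repeat clients but no between-site variation in the before-after change; if fitted that way, its intervals are too narrow to the extent that services change differently

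*Protocol article*

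**What the plan says.** The Analysis section plans a descriptive comparison of the periods and also "multi-level logistic regression models clustered on site and allowing for participants who are active in both periods". It responds to the small number of services by promising cautious interpretation with weight on direction and magnitude. It names no site-by-period term, random period slope, cluster-robust variance or small-sample correction.

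On the number of services, Step 1 says "A minimum of six services (two per jurisdiction) will be recruited" and the Sample size section says "Allowing up to 12 clusters before and after".

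On how alike the services will be, Step 2 says "There will be no predetermined list of strategies; all ideas will emerge through co-design to support local needs". Improving data support is a common focus, but "Strategies to achieve this will vary depending on local systems and capacity". Step 3 lets each service choose and adapt its approach, and its examples include auditing local records against the national register and correcting them. The Limitations section gives data cleaning priority only where it can be done. The Cervical screening data section lets each service choose its data pathway.

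The Sample size section starts from "80% power (2-alpha = 5%) and a conventional non-clustered design, would require 91 women and people with a cervix per arm". It then takes an ICC of 0.1 and 50 people per cluster per period, which "would give a design effect of 5.9".

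**The concern.** In a before-after comparison within the same services, a site intercept absorbs stable differences in level, and these largely drop out of the contrast. The site-level uncertainty that remains is the variation in change from one service to another. A model with site and person effects only sets that variation to zero and treats clients as independent replicates of one common change.

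This protocol gives concrete reasons to expect variation. Services run different strategies. Register-based correction of records can move recorded screening status at one service and not at another. The data source may also differ. A pooled interval that ignores this would overstate how precisely the change is known. The plan wants the modelled result read for direction and magnitude, so the interval should have the coverage it claims.

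**Working it through.** **1. The plan's sample size reproduces.** A comparison of 20% with 40% at 80% power and 5% two-sided needs 91 per arm with a continuity correction (82 without). The design effect is 1 + (50 - 1) × 0.1 = 5.9. The total is 2 × 91 × 5.9 = 1073.8, which rounds up to the stated 1074.

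**2. What that design effect implies for paired sites.** Let ρ be the ICC, m the number per site-period, and c the correlation of a site's effect between periods. For the same sites measured twice, the variance of the before-after difference relative to simple random sampling is

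(1 - ρ) + mρ(1 - c) = 0.9 + 5(1 - c).

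- c = 1, as in a site-intercept-only model: 0.9
- c = 0.9: 1.4
- c = 0.8: 1.9
- c = 0.5: 3.4
- c = 0: 5.9

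The stated 5.9 therefore gives no credit for pairing, whereas a site-intercept-only model takes full credit.

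**3. Effect on the interval.** Let τ be the SD of site-specific change in log-odds. The documents do not give it, so a range is shown. For k sites:

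- Model variance (site intercept only): w/k, with w = 1/[m p0(1 - p0)] + 1/[m p1(1 - p1)]
- True variance: (w + τ²)/k
- Ratio of true to model standard error: √[(w + τ²)/w]. The number of sites k cancels.

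Inputs: prevalence near 50%, from the Sample size section's share of under-screened clients; m = 120, the minimum number of active clients in Step 1, because the primary denominator is all screen-eligible clients; and m = 50 from the Sample size section. Then w = 2/(120 × 0.25) = 0.0667, or 2/(50 × 0.25) = 0.16. Example: τ = 0.3 and m = 120 give √[(0.0667 + 0.09)/0.0667] = 1.53, and 1.96/1.53 = 1.28 corresponds to 80% coverage.

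The type I error columns come from a simulation of 500 runs per cell (Monte Carlo error about 1 percentage point at 5%). It used a random-intercept logistic model with a Wald test, an average change of zero and a site SD of 0.6, since √[(0.1/0.9) × π²/3] = 0.605.

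| τ (log-odds) | SE ratio, m = 120 | 95% CI coverage, m = 120 | Type I error, m = 120 (6 / 12 sites) | 95% CI coverage, m = 50 | Type I error, m = 50 (6 / 12 sites) |
|---|---|---|---|---|---|
| 0 | 1.00 | 95% | 4.4% / 4.8% | 95% | 5.2% / 3.2% |
| 0.2 | 1.26 | 88% | 13.4% / 11.8% | 92% | 6.4% / 6.0% |
| 0.3 | 1.53 | 80% | 19.6% / 20.6% | 88% | 10.6% / 12.0% |
| 0.5 | 2.18 | 63% | 33.8% / 35.0% | 78% | 18.8% / 23.6% |

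Near 50% prevalence, τ of 0.2, 0.3 and 0.5 is an SD of roughly 5, 7.5 and 12.5 percentage points in the change (0.25 × τ).

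The result is not tied to a null average. With 20% before and 40% after, coverage at m = 120 is 90%, 83% and 68% for τ = 0.2, 0.3 and 0.5.

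**4. The alternative.** In the same simulated data, a t-test on site-level log-odds changes with k - 1 degrees of freedom rejected in 3.8-7.2% of runs across all cells.

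**5. Limit of the check.** The simulation treated the two periods as separate people. The participant effect that the plan includes was not modelled.

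**The case against.** The strongest reply is that the defect is read from silence. A multi-level model clustered on site could include a random period slope, or the phrase could mean site-clustered variance, and an analysis plan that is not shown may settle it. This stands in part: the protocol does not exclude site-specific change, so the point is conditional. But the protocol does fix which dependencies the model covers, and the one that matters most for a within-site contrast is not among them. Site-clustered variance would allow for it, but would itself need a small-sample correction with 6 to 12 services.

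Second, the amount of variation is unknown. This stands. Different strategies need not produce very different changes, and with τ = 0 the error is nominal. Between-period correlations of 0.5 or 0 are extreme for a stock measure with partly the same clients.

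Third, if no strategy worked anywhere, differences in strategy would create no variation. That is fair for strategy effects alone. Data cleaning and data source can still move recorded status differently by service, and the loss of coverage also arises when the average change is real.

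Fourth, services are sampled purposefully, so the average change in these particular services is a defensible target, for which between-site variation need not enter the interval. That is coherent if declared. The article, however, wants its findings to inform national scale-up, which asks about services beyond those studied.

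Fifth, the plan already reports descriptively by service and reads the model cautiously. This softens the consequence but does not widen an interval.

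A reader might also infer that the sample size and the model contradict each other. The documents do not support that: the Sample size section states no between-period correlation, and ignoring pairing is a common conservative simplification. All that can be said is that the two do not rest on the same variance structure.

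**Conclusion.** The point holds in conditional form. As described, the model allows for site and repeat clients and names no between-site variation in change, in a design that makes such variation likely. If it is fitted with site and person effects only, the pooled intervals are too narrow to the extent that services change differently. At the minimum service size the consequence is already material at τ = 0.2; at 50 per site-period it becomes so at about 0.3. These figures rest on an assumed τ, prevalence near 50%, and separate people in each period.

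Two stronger readings are tempting and not supported. One is that the intervals are certain to be too narrow, or that the variation must be large: the documents quantify no variation. The other is that having only 6 to 12 services causes the problem: the standard-error ratio does not depend on the number of services, and more services alone would not cure it. The small number matters for a different reason: once between-site variation is estimated, the interval needs a small-sample correction.

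**What to change.** State in the Analysis section that the pooled before-after effect will be estimated in one of two ways:

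- from each service's before-after change, pooled with a t interval on k - 1 degrees of freedom; or
- from the logistic model with a random site-by-period (period slope) effect and a small-sample correction.

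Report the pooled absolute difference with the spread of change across services beside it. The service-level data at T0 and T1 listed in Table 1 already allow this. If the site-level route is chosen, say whether services are weighted equally or by size.

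The cost is about one sentence in the plan and slightly more analysis work. No new data are needed. The downside is wider intervals.
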